## Abstract

**Background:**

Subthreshold depression (StD) is a condition that significantly influences the mental health and quality of life of college students and increases the risk of developing major depressive disorder (MDD). Exercise therapy has been found to be effective, but may not be enjoyable for everyone. exergames, as a form of exercise therapy, address the limitations of traditional exercise by incorporating gaming elements to make physical activity more entertaining and interactive. Currently, the Nintendo Switch is one of the most widely used exergame devices.

**Aims:**

To explore the effectiveness of a Nintendo Switch-based exergame intervention on college students with StD compared to a control group, and to analyze their perceptions of the program.

**Methods:**

This study will employ an explanatory sequential design, starting with a quantitative evaluation using a randomized controlled trial (RCT), followed by a supplementary qualitative study. College students identified as having StD will be randomly allocated in a 1:1 ratio into the exergame intervention group (EIG) or the control group (CG). College students in the EIG will participate in a Nintendo Switch-based exergame program for 8 weeks, with 2–3 sessions per week, lasting 50–60 min each. Participant outcomes in both conditions will be assessed at pre-intervention (T_0_, week 0), post-intervention (T_1_, week 8), 1 month after the intervention (T_2_, week 12), and 2 months after the intervention (T_3_, week 16), and a generalized linear mixed model will be used for analysis. In the qualitative part of this study, interviews will be conducted with college students with StD from the EIG at T_1_ to explore their experiences of receiving the intervention, and content analysis will be applied to the data collected.

**Discussion:**

Nintendo provides a user-friendly platform for college students with StD to engage in electronic gaming. Limited research has explored the mental health outcomes of interventions using this type of technology in young people with StD. If the exergame program proves to be effective, it could offer a convenient and feasible intervention for further enhancing the psychological well-being of college students.

**Clinical trial registration:**

This study was registered in the Chinese Clinical Trial Registry (number: ChiCTR2300068970) on 2nd March 2023.

## Introduction

1

Subthreshold depression (StD), considered to be the precursor stage of major depressive disorder (MDD) (1), is defined as the simultaneous presence of 2 to 4 depressive symptoms for at least 2 weeks causing significant functional impairment in daily activities or social relationships, without meeting the full diagnostic criteria for a depressive disorder (2). The prevalence of StD ranges from 1.50% (3) to 41.27% (4) in adults. In college students, a prevalence of 40.8% has been reported (5), significantly exceeding the one for the general population (6). In this population, StD has been associated with different factors including interpersonal difficulties, and academic and employment pressures (6). StD can significantly impact the mental health and social functioning of the affected individuals (7), and has been linked with an increased risk of suicide (8).

Previous studies have reported an association between StD and adverse clinical outcomes including MDD, neurotic symptoms, and geriatric patients. Lyness et al. (9) conducted a cohort study including 622 elderly patients, and found that individuals with StD had a 5.5-fold increased risk of developing major depression 1 year after baseline evaluation, compared with non-depressed patients. An et al. (10) found that individuals with StD scored significantly higher in obsessive-compulsive disorder and anxiety. Goldney et al. (11) found that StD can lead to sexual dysfunction and suicide, resulting in a decline in the quality of physical, psychological and social relationships (12). In 2022, the Ministry of Education of the People’s Republic of China further emphasized the need to strengthen students’ mental health education, and to improve identification and prevention (13). Therefore, identifying effective interventions for StD to prevent its development into MDD has become a major public health priority.

In many countries, the management and intervention approaches for StD typically involve a comprehensive, multidisciplinary, and multifaceted treatment approach, encompassing both pharmacological interventions (PIs) and non-pharmacological interventions (NPIs). Currently, pharmacological interventions specifically tailored for StD are scarce. Although certain studies have demonstrated that antidepressants can mitigate depressive symptoms in adults with StD (14), there is not enough evidence to recommend the widespread use of antidepressants for the treatment of StD (15). In addition, a recent study has shown a significant effect of NPIs in preventing the onset of MDD and improving depressive symptoms (7). Exercise therapy, recommended in the UK’s National Institute for Health and Care Excellence (NICE) guidelines (16, 17), is characterized by lower costs, fewer side effects and rapid effectiveness compared to other treatments, and has been shown to be effective in reducing depressive symptoms (18). However, some studies suggest that traditional exercise can be considered monotonous and insufficiently stimulating, often lacking variety, reducing individuals’ willingness to participate and adhere in the long-term (19).

Exergames, a type of exercise therapy, overcome the limitations of traditional exercise therapy by incorporating gaming elements. By providing more stimulating and personalized exercise options, exergames enrich the forms and contents of exercise with fun, interaction, and pleasure, enhancing individuals’ motivation to participate in physical activity and improving the effectiveness of exercise in promoting health (20). Nintendo is one of the most popular tools in neural rehabilitation, favored for its unique interactivity and somatosensory controllers, and has been found to be safe (21, 22), useful (22–24), and feasible (22), as well as enjoyable and motivating (21, 22, 24). Studies have shown that Nintendo-based exergames can significantly improve depressive symptoms in older adults (25, 26), but there is little evidence in college students, who represent a vulnerable population. Although a study developed in China reported that exergames (27) could improve the depression in college students, the exergames were limited to a simple combination of sports and games.

Meanwhile, an in-depth understanding of the experiences of individuals with StD participating in exergames will help improving and promoting these intervention programs, as well as encouraging their use and acceptability. Wingham et al. conducted a qualitative study exploring the acceptability of using the Nintendo Wii Sports games in stroke survivors and showed the Wii was acceptable to these patients in home-based rehabilitation (28). Glännfjord et al. examined perceptions of using Wii Sports Bowling by older adults, who described it as enjoyable and a social activity (29). Overall, research exploring the experiences of using exergames in college students with StD is insufficient.

The main aim of this study is to explore the therapeutic effects and the experiences of using exergames in college students with StD. An explanatory sequential design will be used, starting with a randomized controlled trial (RCT) investigating the impact of a Nintendo Switch-based exergame intervention on mental health outcomes (depression, anxiety, sleep quality) in a group of college students with StD. For this, a personalized exergame program based on the characteristics, needs and preferences of college students with StD will be considered to tailor the intervention to their unique needs and stimulate their engagement. Subsequently, qualitative surveys will be conducted to gain an in-depth understanding of college students’ subjective experiences of participating in this exergame intervention, in particular the benefits arising from the intervention as well as the influencing factors for participation, which will help understanding the mechanisms behind the therapeutic effects. This information will provide a basis for optimizing, refining, and promoting exercise game intervention programs.

We hypothesize that participants in the exergame intervention group (EIG) will experience an improvement of depressive and anxiety symptoms, and sleep quality, compared to those in the control group (CG). Furthermore, we anticipate that these improvements will be maintained at 2-months follow-up.

## Methods

2

### Study design

2.1

This mixed methods study will comprise an assessor-blinded, parallel-group, randomized controlled trial and a qualitative study. Such a design is supported by the Medical Research Council’s guidance for evaluating complex interventions (30). The study will employ an explanatory sequential design, starting with a quantitative outcome-based evaluation exploring treatment effects, and followed by a qualitative study to gain insights into participants’ perceptions of the treatment. The qualitative study will allow understanding the real experiences of students with StD participating in the intervention and the mechanisms behind the treatment (31). The study design is illustrated in Figure 1.

**Figure 1 fig1:**
[figure not shown]
Study design flowchart.

### Sample size and power calculations

2.2

For the quantitative part of this study, an *a priori* power analysis was conducted using G*power 3.1.9.7. A recent meta-analysis found a significant effect of exergame-based exercise training on depressive symptoms, with a moderate effect size of 0.69 (19). Assuming an attrition rate of 10%, a sample size of 76 participants (38 participants per arm) will be required to provide an 80% power to detect an effect size of at least 0.69 at a 5% significance level in a 2-arm trial.

For the qualitative component of this study, purposive sampling will be used to select college students with StD who completed the 8-week exergame intervention (excluding dropouts). The number of interviews will be determined by data “saturation” (32).

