### Statistical analysis

2.8

For quantitative analysis, Epidata 3.1 (Epidata Association) will be used for double data entry and SPSS 26.0 (International Business Machines Corporation, IBM) will be used for data analysis and processing. Descriptive statistics will be used to describe participants’ characteristics and mental health outcomes. For continuous variables, the Shapiro–Wilk test (S-W test) will be used to assess normality. Depending on the results of the S-W test, the mean and standard deviation or the median and the interquartile range will be used for descriptive statistics. For categorical variables, frequencies and percentages will be reported. Independent samples t-tests, Mann–Whitney U tests and χ^2^ tests will be used to compare outcome results and baseline data. Paired sample t-tests or non-parametric rank sum tests will be used to compare the outcomes within the group. To analyze between-group differences, a two-independent sample t-test or a Mann–Whitney U rank sum test will be used. The changing trend of the outcome indicators of the study subjects will be measured between T_0_, T_1_, T_2_, and T_3_; the inter-group factor will be the subgroup (EIG and CG), the intra-group factor will be the measurement time point (T_0_, T_1_, T_2_, and T_3_), and the interaction will be the group × time point. A generalized linear mixed model will be used for analysis. The significance level of all the above statistical tests will be set at *p* ≤ 0.05, indicating a significant statistical difference.

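### The 80% power in section 2.2 is that of a single-visit two-sample t-test and does not carry over to the four-visit group × time test of the mixed model named in the abstract

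*Protocol article*

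**What the plan says.** Section 2.2 takes an effect size of 0.69 from a meta-analysis and allows for 10% attrition. It concludes that 76 participants, 38 per arm, are "required to provide an 80% power to detect an effect size of at least 0.69 at a 5% significance level in a 2-arm trial". It names no test, outcome scale, visit or between-visit correlation.

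The abstract lists assessments at T0, T1, T2 and T3 and names one quantitative analysis: "a generalized linear mixed model will be used for analysis".

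Section 2.8 is wider. It plans a two-sample t-test or Mann–Whitney test for between-group differences. It then describes the change over T0 to T3 with group as the between-subject factor and the four visits as the within-subject factor: "the interaction will be the group × time point. A generalized linear mixed model will be used for analysis". It does not say which of the two analyses decides the trial, or at which visit the t-test is made.

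**The concern.** A reader who puts the abstract next to section 2.2 will attach the 80% to the mixed model. The treatment term of that model, as section 2.8 sets it out, is group × time over four visits, with T0 as one of the outcome occasions. With two groups and four visits this is a 3-df test. Its power depends on the correlation between visits and on how the effect runs over T1 to T3, and section 2.2 uses neither.

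If the interaction is read as the trial's result, its chance of detecting the effect the trial was sized for is unknown from the document and may be well under 80%. A non-significant interaction could then be over-read as evidence that the exergame programme does not work.

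**Working it through.** **Inputs from the document.** Effect size 0.69, 5% level, 80% power, 10% attrition and 38 per arm (section 2.2); 1:1 allocation (section 2.4); four visits (Table 2); group, time and group × time (section 2.8).

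**Assumed, because the document is silent.** Two-sided testing; SD 1 at every visit; 34 evaluable per arm; 0.69 as the T1 difference unless noted; the correlation ρ, its structure and the effect profile.

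**Step 1: reproduce the stated figure.** For a two-sample t-test the noncentrality is d·√(n/2) on 2n − 2 df.
- n = 33 per arm: power 78.8%.
- n = 34 per arm: 0.69 × √17 = 2.845 on 66 df, power 80.05%.
- Attrition: 34/0.9 = 37.8, rounded up to 38 per arm, 76 in total.

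This matches exactly. A one-sided test would need 27 per arm, 30 after attrition and 60 in total, so the calculation was two-sided. No repeated-measures input is needed to reach 76.

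**Step 2: power of the 3-df group × time test.** Let δ be the group differences at T0 to T3, R the correlation matrix and C the three contrasts of T1, T2 and T3 with T0. The noncentrality is

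λ = (n/2)·(Cδ)′(CRC′)⁻¹(Cδ),

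referred to a noncentral F on 3 and 3(2n − 2) = 198 df under compound symmetry, or 3 and 2n − 4 = 64 df under AR(1).

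Under compound symmetry λ reduces to (n/2)·Σ(δ − mean δ)²/(1 − ρ):
- Constant effect (0, 0.69, 0.69, 0.69): 17 × 0.3571/(1 − ρ) = 6.07/(1 − ρ).
- Fading effect (0, 0.69, 0.46, 0.23): 17 × 0.2645/(1 − ρ) = 4.50/(1 − ρ).

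| Structure and profile | ρ = 0.3 | ρ = 0.4 | ρ = 0.5 | ρ = 0.7 |
|---|---|---|---|---|
| Compound symmetry, constant | 68% | 76% | 84% | 97% |
| Compound symmetry, fading | 54% | 61% | 70% | 91% |
| AR(1), constant | 57% | 61% | 68% | 88% |
| AR(1), fading | 50% | 57% | 66% | 90% |

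Simulation of 20,000 trials per cell under compound symmetry at ρ = 0.3, 0.5 and 0.7 gave 0.685, 0.834 and 0.974 (constant) and 0.542, 0.700 and 0.911 (fading), with null rejection 0.050.

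The profile matters in both directions. An effect growing as 0.23, 0.46, 0.69, so that 0.69 is reached only at T3, has about 36–39% power under AR(1) at ρ = 0.3–0.5.

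**Step 3: 1-df contrasts at T1, 34 per arm.**
- T1 minus T0 change, effective size d/√(2(1 − ρ)): 66%, 80% and 95% at ρ = 0.3, 0.5 and 0.7. It equals the stated 80% at ρ = 0.5 only because 2(1 − 0.5) = 1.
- T1 with T0 as a covariate, effective size d/√(1 − ρ²): 0.723 and 84% at ρ = 0.3; 0.797 and 90% at ρ = 0.5. At ρ = 0 it returns to 0.69 and about 80%.

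**The case against.** The strongest reply is that section 2.8 plans a two-sample t-test for between-group differences, the very test that yields 76, and gives the mixed model another job, the trend over time. This stands. A reader might infer that the 80% belongs to an unplanned test, or that the trial is judged on the interaction. The document supports neither: the t-test is planned, and the abstract names the model without saying which of its terms decides. The reply does not settle the matter, because the t-test sentence names no visit and the abstract gives no other quantitative analysis.

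Second, the range in step 2 rests on inputs from outside the document and straddles 80%. This stands too. Under compound symmetry, power is 84% at ρ = 0.5 with a constant effect and 91–97% at ρ = 0.7. The introduction expects benefit to be maintained at two months, which favours the constant rows. Those still run from 57% to 84% at ρ = 0.3–0.5.

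Third, a reader might argue that entry at CES-D 16 or more lowers the correlation with T0 and so points to the low end. The document does not say that the screening score is the T0 score. Truncation also shrinks the T0 variance, which works the other way. With normal scores, mean 14–18, SD 9 and population correlation 0.5–0.6 (all assumed), the full truncated covariance gives 80–84% for the T1 minus T0 contrast. For the constant-effect interaction in a compound-symmetric population it gives 86–89%. The argument fails.

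Fourth, a mixed model does not in itself cost power. The mean of the post-baseline visits minus baseline has 83–93% at ρ = 0.3–0.5 for a sustained effect. That is correct, and it is why the remedy stays within the model. Finally, sizing on a simple comparison is common, and an article may leave a correlation to a fuller document. The point here is what a stated figure refers to, not a missing detail.

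**Conclusion.** The point holds in a limited form. The 80% is correct for an unadjusted two-sided two-sample t-test of one score at one visit with 34 evaluable per arm. It is not a property of the 3-df group × time test in the model that the abstract names. For that test, power is about 54–84% (compound symmetry) or 50–68% (AR(1)) at correlations of 0.3–0.5 for constant or fading effects, and 91–97% under compound symmetry at 0.7.

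Two stronger readings are not supported. One is that the trial is underpowered: the correlations that would show it are not in the document, and other planned or available contrasts reach 80%. The other is that the loss is greatest when benefit fades after week 8: an effect growing to T3 under AR(1) does worse, at about 36–39%. The supportable statement is that the interaction's power depends on unstated inputs and may lie on either side of 80%.

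**What to change.** In section 2.2, state that the 80% refers to a two-sided two-sample comparison of one named depression score at one named visit, with 34 evaluable per arm.

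In section 2.8, make the deciding analysis a 1-df EIG versus CG contrast at that visit, estimated from the mixed model with the T0 score as a covariate and not as one of the outcome occasions. Keep the 3-df group × time test as supportive. The contrast has 84% power at correlation 0.3 and 90% at 0.5, so the stated 80% is met by the analysis that decides. For the profiles tried at those correlations, this is more than the 3-df interaction offers.

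The cost is protocol wording and one recalculation. T0 is already collected and no extra participants are needed. The small downside is that the interaction becomes supportive.

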#### Qualitative data collection

2.6.2

The college students with StD who have completed the 8-week Nintendo Switch-based exergame intervention will be invited to participate in one-on-one, face-to-face semi-structured interviews to explore their experiences of taking part in the intervention. Table 3 shows the details of the interview outline.

**Table 3 tab3:** Semi-structured interview outline.

Number	Questions
1	What was your initial reason (or motivation) for participating in the exergame intervention? Please describe your reasons in order of importance.
2	What are your feelings after attending the exergame intervention?
3	What challenges have you encountered when participating in the exergame intervention? What was the biggest challenge? How was it resolved? Please provide examples and details.
4	Would you like to participate in other activities similar to the exergame intervention in the future? Would you recommend the exergame intervention to other people? Please state specific reasons.
5	What traditional exercise activities have you participated in before? In what ways do you think this combination of exercise and play could benefit you more than traditional exercise methods?
6	What kind of support and assistance in the exergame intervention would you like to receive in the future? Please be specific about what you think needs to be improved and refined.
7	Is there anything else you would like to add to today’s conversation?

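### The interviews sample completers only, so they cannot hear first-hand why students stopped, and half of one interview question is leading

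*Protocol article*

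**What the plan says.** Section 2.2 (Sample size and power calculations) sets a purposive sample of students "who completed the 8-week exergame intervention (excluding dropouts"), with the number of interviews decided by saturation. Section 2.6.2 (Qualitative data collection) applies the same restriction: the students "who have completed the 8-week Nintendo Switch-based exergame intervention will be invited to participate in one-on-one, face-to-face semi-structured interviews". The abstract fixes arm and timing: "interviews will be conducted with college students with StD from the EIG at T_1_ to explore their experiences of receiving the intervention".

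The purpose is described in two places. The Introduction says the interviews concern students' subjective experience, "in particular the benefits arising from the intervention as well as the influencing factors for participation", and that the results will be used to improve and promote the programme. Section 2.1 (Study design) speaks of "understanding the real experiences of students with StD participating in the intervention and the mechanisms behind the treatment".

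Table 3 lists seven interview items. Item 5 first asks which traditional exercise the student has done, then asks: "In what ways do you think this combination of exercise and play could benefit you more than traditional exercise methods"? Item 3 is open about difficulties: "What challenges have you encountered when participating in the exergame intervention? What was the biggest challenge? How was it resolved"?

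**The concern.** A sample meant to show what influences participation is selected on participation itself. Completers can report what drew them in and which obstacles they overcame. They cannot report first-hand the obstacles that made someone else stop, and the protocol gives no reason for leaving those students out.

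This matters because engagement is central to the study's rationale. The Introduction favours exergames because traditional exercise may weaken the willingness to take part and persist. Section 2.6.1.6 (Adherence) sets a formal practice-time standard. The Discussion lists sustained motivation among the challenges that could weaken the treatment effect. In an explanatory sequential design the interviews are there to help explain the quantitative results. Dropout will be one of those results, and the sampling rule removes the students best placed to explain it.

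The second half of item 5 leans the same way. It takes a benefit over traditional exercise as given and asks only what form it takes, so a student who saw no difference, or preferred ordinary exercise, has to contradict the question in order to answer it.

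**Working it through.** The point rests mainly on setting passages against each other. Arithmetic serves only to size the excluded group.

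**Step 1: reproduce the plan's own figure.** Inputs from section 2.2: effect size 0.69, power 80%, significance level 5%, attrition 10%. Two-sided testing is assumed, because the section does not state sidedness.
- A two-sample t-test calculation with the noncentral t distribution gives 33.96, so 34 per arm (power 0.8005).
- Allowing for attrition: 34 / (1 − 0.10) = 37.8, so 38 per arm and 76 in total.

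This matches the stated 76. The sample size is not in question.

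**Step 2: size the excluded group.** Apply the 10% to the exergame arm.
- Expected dropouts: 38 × 0.10 = 3.8. Left for interview: 38 − 3.8 = 34.2.
- Chance of at least one dropout, treating students as independent: 1 − 0.90^38 = 0.98.
- The 10% is a planning figure for the whole trial, so the arm's own rate may differ. Over an assumed range of 5% to 30%, the expected number excluded runs from 38 × 0.05 = 1.9 to 38 × 0.30 = 11.4.

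The group is small but almost certain to exist.

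**Step 3: compare the aim with the sampling frame.**
- *Benefits and experience of the programme* (Introduction, section 2.1): students who received all of it are a reasonable source.
- *Influences on participation* (Introduction): completers can supply reasons for joining and staying, and difficulties they overcame. Reasons for stopping are out of reach.

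One part of the stated aim is therefore only partly reachable.

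**Step 4: check what completion means.** Section 2.6.1.6 derives 140 min/week × 8 = 1,120 min and 1,120 × 0.80 = 896 min. Section 2.2 does not say whether completing the intervention means reaching 896 minutes or simply remaining to week 8. The two can differ: the lowest schedule used in that section's own derivation gives 100 min/week × 8 = 800 min, below 896. A student with low practice time may or may not be eligible for interview, depending on the reading.

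**Step 5: read the guide item by item.**
- Item 1 asks about motivation for joining.
- Item 2 asks about feelings.
- Item 3 asks about challenges.
- Item 4 asks about willingness to repeat or recommend, with reasons.
- Item 5 has a neutral first half and a second half that presumes superiority.
- Item 6 asks about support and needed improvements.
- Item 7 invites anything else.

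So half of one item in seven is leading.

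**The case against.** The strongest reply is that the interviews are about the experience of receiving the programme, and those who received all of it are the right people to ask. Explaining discontinuation is nowhere stated as an aim, and the restriction is stated openly and consistently. Much of this stands. It does not cover the Introduction's separate mention of influences on participation, which go beyond the views of those who stayed.

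Several stronger readings are tempting, and the document does not support them.
- *The interviews cannot meet their aim.* Items 1, 3, 4 and 6 ask openly about motivation, challenges, willingness and improvement, so completers can report both facilitators and barriers.
- *Any conclusion that the programme is easy to keep up would rest on adherers alone.* The Conclusion ties that expectation to proven effectiveness, not to the interviews, and adherence is measured separately as practice time.
- *The excluded students are those whom the programme failed.* Their reasons are unknown. The Discussion mentions busy schedules and academic pressure as obstacles to taking part, and reasons of that kind need not reflect on the programme.
- *Item 5 tilts the whole guide.* Its effect is confined to answers to that half-item.
- *Item 5 is invalid because the trial has no traditional-exercise arm.* It asks for a personal impression, which needs no randomised comparator, and the contrast is part of the study's rationale. The fault lies in the one-sided wording.

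Two practical objections also stand. Inviting students when they stop would depart from the T1 timing in the abstract. Choosing interviewees by their change in CES-D is not needed, and it would raise a question about the blinding in section 2.4; the fix avoids it.

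**Conclusion.** The concern holds in a limited form. As designed, the interviews can describe influences on participation among completers only and cannot hear first-hand why students stopped. The second half of item 5 is leading.

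The size is modest: about 4 of 38 exergame students at the assumed 10% attrition, on the assumption that the trial-wide figure applies to that arm. Because interview numbers are set by saturation, not all 38 would be interviewed anyway, but even a few contrasting cases could be informative. The direction of any resulting bias cannot be established from the document; a tilt towards more motivated or satisfied students is plausible, not demonstrated.

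The change is worth making because one stated purpose of the mixed-methods study is only partly achievable and the remedy is cheap. The quantitative outcomes, the randomised comparison and the sample size are not affected.

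**What to change.** 1. In section 2.2, replace the exclusion of dropouts with a purposive stratum of exergame students who stopped early or fell below the 896-minute standard. Make section 2.6.2 agree. Record the two reasons for inclusion separately, and state what counts as having completed the intervention.
2. Invite these students at T1 or at the time they stop, and amend the interview timing in the abstract to match.
3. If such students cannot be interviewed, restrict the aim in the Introduction, and any conclusions about participation, to students who completed the programme.
4. Reword the second half of item 5, for example: *How did this combination of exercise and play compare with traditional exercise for you: better, worse or no different, and why?*

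Rewording item 5 and restricting the aim cost nothing. The extra stratum costs a few more interviews by the same team: about 4 early stoppers at 10% attrition, plus any students with low practice time who are chosen. Some who stopped will decline, so the number invited and the number interviewed should both be reported.
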